## Introduction

### Background

Over the past decade in Indonesia, there has been little change in child stunting, with the national prevalence of stunting estimated as 37% of children aged under 5 years [1,2]. This high level of growth failure has profound adverse consequences for the physical and economic development of affected children, their communities, and the country overall [3-7]. Growth faltering among Indonesian children starts in utero and is associated with low maternal height and poor nutritional status [8-15]. Among children in Indonesia, as elsewhere, 2 major determinants—undernutrition and infections—broadly account for postnatal deterioration in growth [10,15-20]. In studies examining risk factors for child stunting in Indonesia, lower maternal education and household wealth, including lower expenditure on foods from animal sources, are associated with a higher prevalence of child stunting [15,18,19,21].

Presidential Decree Number 42/2013 on The National Movement for the Acceleration of Nutrition Improvement prioritized the improvement of nutritional status in the first 1000 days of life, with the stunting of children aged <5 years as a key indicator. The decree addresses 4 main strategies. The first is to make nutritional improvements as the mainstream of the development plan. The second is building capacity and increasing human resource competence to respond to nutritional needs in all sectors. The third is to promote effective evidence-based interventions to improve nutrition. The fourth is increasing community participation in nutrition programs. The Government of Indonesia prioritized stunting reduction as part of the Ministry of Health Strategic Plan 2015-2019 and aimed to reduce the prevalence of stunting among children aged <2 years from 33% in 2013 to 28% in 2019 [22].

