#### Anthropometry

Trained field workers will collect measurements of weight, recumbent length in infants, height in mothers, and mid-upper arm circumference in pregnant women using standard methods and equipment [39,40]. We will standardize the measurements of the anthropometry field workers using established methods before and during data collection [39]. In both the cross-sectional and cohort evaluations, 2 field workers will collect duplicate measurements of the weight and length of children aged <2 years. The field workers will take a third measurement if the difference between the first 2 measurements exceeds a predetermined allowable limit (see details below).

We will calculate the Z scores for infant length-for-age and weight-for-length using the 2006 WHO Child Growth Standard [41], and we will define stunting as a low length-for-age or <−2.00 SD from the reference mean and wasting as low weight-for-length or <−2.00 SD. We will collect mid-upper arm circumference from pregnant mothers and define it as low if <23 cm [42].

The field workers will collect all anthropometry data using in-field digital data capture on tablets with routines that immediately calculate Z scores and provide them with a warning about extreme values and the need for remeasurement to check for potential errors (ie, if first and second measurement differed by >0.7 cm for length and by >0.1 kg for weight). We will refer to children with very low weight-for-height (Z score<−3) to their local community health center for assessment and treatment of severe acute malnutrition.

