Based on this calculation, the sample size required is 1392 mother-infant dyads from each group of 6 subdistrict clusters or approximately 232 mother-infant dyads per subdistrict cluster. We will round this up to 2800 mother-infant dyads per cross-sectional survey or 234 per subdistrict cluster. This sample size will provide 80% power assuming a Z score SD of 0.975 and 5% level of significance to detect a 0.15 Z score difference in height-for-age Z scores [49] between the intervention and the control groups in the end-line survey. Therefore, for the cross-sectional evaluation, we will select 2800 mothers of children aged 0-23 months and an additional 400 pregnant women from 12 subdistricts within the Sidoarjo and Malang districts.

For the cohort evaluation, to detect a difference in mean length-for-age Z score between the experimental and control groups at an end line of 0.35 Z score [50], assuming 80% power and 5% level of significance, with a design effect of 1.5 (see above), we will require a sample size of 272 mother-infant pairs in each of the intervention and comparison groups. Assuming a dropout rate of 25%, we need to recruit 680 mother-infant pairs (56-57 per subdistrict cluster).

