### Statistical Methods

The intention-to-treat principle will guide our data analysis, and we will include data from all participants even if they do not participate in all interventions. We will apply the guidelines of the Consolidated Standards of Reporting Trials statement for clustered randomized trials in the analysis and presentation of the results. We will conduct analyses at the woman or infant level adjusted for cluster randomization. Initially, we will assess the effectiveness of randomization by comparing potential confounding factors in both treatment groups. We will apply statistical tests with χ^2^ tests for categorical variables and an adjusted Wald test or the Fisher exact test for continuous variables to assess for any significant difference between treatment groups. *P* values <.05 will be considered to indicate a statistically significant difference between the groups. For selected dietary analyses of continuous variables, we will use the nonparametric rank order statistic, Somers’ D [51] (corresponding to rank-sum tests), as it can adjust for the cluster sampling design.

We will calculate frequency and percent distributions for categorical variables and mean and SD or median and interquartile range for continuous variables. We will characterize the dietary intake by age group, breastfeeding status (for infants aged 12-23 months), and intervention and comparison groups. We will generate medians and interquartile ranges for dietary intake distributions that are not normally distributed. We will plot the frequency distribution of IYCF practices by child age. We will also plot the frequency distribution of Z score indices (Z score curves) in 0.25 Z score intervals using a Lowes function to smooth the curves, and we will compare these distributions with the growth standard distribution. We will repeat these plots broken down by treatment groups.

For the cross-sectional evaluation, the primary analyses will compare the prevalence of stunting (low length-for-age<–2 Z score) and the 95% confidence intervals in each treatment group adjusted for clustering and any imbalanced baseline characteristics.

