For the cohort evaluation, the models will include the treatment group as a fixed effect, the community cluster as a random effect to account for the cluster effect, and the impact of the interventions over time by testing for an interaction between time and intervention group. We will conduct analyses to identify the subgroups (eg, level of maternal education or household wealth categories) that modify the response to the intervention. We will check the model assumptions and make appropriate adjustments to the analysis where necessary. Secondary analyses will examine each outcome variable (length-for-age Z scores, feeding patterns, and mean nutrient intakes), taking into account the repeated measurements within children by using separate mixed models.

Linear mixed models will be used for continuous outcomes (eg, length-for-age Z scores), and generalized linear mixed models will be used for noncontinuous outcomes (eg, mixed logistic models for binary outcomes, such as, percentage exclusively breastfeeding). Models will include intervention or comparison groups as a fixed effect, infants as a random effect to account for repeated measurements, and community cluster as a random effect to account for cluster effects. We will use Stata V.15 (Stata Corp 2017; Stata Statistical Software: Release 15; Stata Corp LP) for all analyses.

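### The cohort length-for-age model names no baseline covariate, although maternal height is identified as prognostic and already measured; prespecifying it would gain a little precision at almost no cost.

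*Protocol article*

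**What the plan says.** Statistical Methods gives the cohort model twice. First: "For the cohort evaluation, the models will include the treatment group as a fixed effect, the community cluster as a random effect", with a time-by-intervention interaction. Then, for the mixed models: "Models will include intervention or comparison groups as a fixed effect, infants as a random effect to account for repeated measurements", again with a cluster random effect. Neither statement lists a baseline covariate. Maternal education and household wealth enter the cohort analysis only as possible effect modifiers.

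The cross-sectional analysis does have an adjustment rule: prevalences are to be "adjusted for clustering and any imbalanced baseline characteristics". Nothing equivalent is stated for the cohort. The nearest sentence is "We will check the model assumptions and make appropriate adjustments to the analysis where necessary", which concerns model assumptions and names no variable.

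On maternal height, the Background says that growth faltering in Indonesian children "starts in utero and is associated with low maternal height and poor nutritional status". The Anthropometry section states: "Trained field workers will collect measurements of weight, recumbent length in infants, height in mothers, and mid-upper arm circumference in pregnant women". Outcome Measurements and Types of Information Collected both include maternal anthropometry in the cohort data.

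The cohort sample size is set "to detect a difference in mean length-for-age Z score between the experimental and control groups at an end line of 0.35 Z score", with 80% power, 5% significance and a design effect of 1.5, giving 272 pairs per group.

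**The concern.** Mean length-for-age Z is the primary outcome of the cohort evaluation, and the trial has at most 12 randomised units. With so few clusters, prognostic information measured before treatment is a cheap source of precision, and the article itself points to one such variable. Constrained randomization balances distance to care, weighing coverage, underweight prevalence, health-post density and low-income families. It does not balance maternal stature, so the arms could differ on it by chance.

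At stake are a modest amount of power for the 18-month contrast and some protection against such an imbalance. Naming the covariate in advance also removes any choice about adjustment once results are visible.

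**Working it through.** **Inputs from the article.** Difference 0.35 Z; two-sided 5% level; design effect 1.5; 272 per group; 12 clusters (6 per arm, Cluster Selection and Design of Randomization). The recruitment target of 680 spread at 56-57 per subdistrict also implies 12, since 680/12 = 56.7.

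**The plan's own figure.** n = 1.5 × 2 × [SD × (1.96 + 0.84)/0.35]². No SD is stated for the cohort. With 0.975, the only SD in the article (given for the survey), n = 183, not 272. Solving for n = 272 gives SD = 1.19. Both values are carried below.

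**Variance split.** Infants per cluster m = 272/6 = 45.3. From 1 + (m − 1)ρ = 1.5, ρ = 0.5/44.3 = 0.0113. If maternal height has correlation r with length-for-age at 18 months, it is credited with removing r² of the within-cluster variance and none of the between-cluster variance:

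SE² = (2/6) × SD² × [ρ + (1 − ρ)(1 − r²)/m]

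Power is from the noncentral t with 12 − 2 = 10 df and noncentrality 0.35/SE. Height is an individual-level covariate and costs no cluster-level df.

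- Unadjusted, SD 1.19: SE² = (0.01596 + 0.03086)/3 = 0.01561, SE = 0.1249, noncentrality 2.80, power 71.4% (80.0% on the plan's normal scale).
- r = 0.3: SE² = (0.01596 + 0.03086 × 0.91)/3 = 0.01468, SE = 0.1212, power 74.0%.

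**Assumed range of r** (the documents give no value):

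| Setting | No covariate | r = 0.2 | r = 0.3 | r = 0.4 |
|---|---|---|---|---|
| SD 1.19, 272 per arm, 12 clusters | 71.4% | 72.6% | 74.0% | 76.1% |
| SD 0.975, 272 per arm, 12 clusters | 86.8% | 87.6% | 88.7% | 90.2% |
| SD 1.19, 329 per arm (mean of 331 and 327 retained), 12 clusters, same ρ | 76.5% | 77.5% | 78.8% | 80.6% |
| SD 1.19, 272 per arm, 6 clusters (4 df, design effect held at 1.5) | 56.4% | 57.5% | 58.9% | 60.9% |

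The gain is positive in every row and lies between about 1 and 5 points.

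**Why an interaction with visit.** A height effect held constant over time drops out of any within-child change, so it would not sharpen the time-by-treatment contrast. To remove variance at 18 months in particular, the height effect must be allowed to differ by visit.

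**The subdistrict baseline mean as a further covariate.** The February 2015 survey measured 2435/12 = about 203 children per subdistrict. Treating them as a simple random sample, the reliability of a subdistrict mean is 0.0113/(0.0113 + 0.9887/203) = 0.70; the multistage sampling would lower it. The term costs one cluster-level df (10 to 9). With SD 1.19 and r = 0.3 for height, height alone gives 74.0%. Adding the subdistrict mean gives 73.0%, 73.9%, 75.7% and 80.1% for assumed true between-cluster correlations of 0, 0.3, 0.5 and 0.8. With 6 clusters (4 df to 3) and a correlation of 0.5, power is about 52-53%, against 58.9% for height alone.

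**The case against.** The strongest objection is that a covariate list is what an article commonly leaves to the analysis plan, and that no sentence here excludes covariates. That bars calling the omission an error, and a reader who infers that the article forbids adjustment goes further than the text. What remains is that the article lists the terms of the cohort model twice and gives an adjustment rule to the survey analysis only. The point is therefore an improvement to a model that is actually stated.

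A reader might also infer that the unadjusted cohort result is biased. It is not: under randomisation with clustering accounted for, leaving out a prognostic covariate costs efficiency, not validity. Constrained allocation on underweight and low-income families already limits some imbalance in prior nutrition, though not in maternal stature.

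A third inference is a loss approaching 9 points, with the subdistrict's baseline mean length-for-age as the remedy. The documents do not support this. The upper end needs an assumed between-cluster correlation of about 0.8, and at 0.3 or below the term adds nothing beyond height or loses power. The number of cohort clusters is also unsettled: Cohort Study Assessment speaks of a subset of clusters, Sampling Procedure of six subdistricts, and the per-cluster figure in Sample Size implies twelve.

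Finally, the calculation is for a single 18-month contrast, which is how the sample size is framed. It does not model the full repeated-measures analysis. That limit stands.

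**Conclusion.** The point holds as a modest efficiency gain. The stated cohort model omits a pre-treatment variable that the article itself calls prognostic and already collects. Adding maternal height gains roughly 1 to 5 points of power for the 18-month contrast: 71% to 73-76% at SD 1.19, and 87% to 88-90% at SD 0.975. These figures assume a correlation of 0.2 to 0.4, a design effect of 1.5 and a t test on 10 df. Neither the correlation nor a cohort SD is in the documents, so the size is indicative; the direction was the same in every setting checked. The calculation also takes height to be available for essentially all cohort mothers, which the article implies but does not state. There is no firm case for the subdistrict baseline mean in the primary model.

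**What to change.** In Statistical Methods, add maternal height and its interaction with visit as prespecified fixed effects in the cohort length-for-age model, whether or not the arms turn out to be imbalanced on it. If the analysis plan already names the covariates, refer to it. If the stated model has already been run, report the height-adjusted result beside it and label it as such.

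Keep the subdistrict's February 2015 mean length-for-age, if wanted, as an optional sensitivity analysis. Do so only after Cohort Study Assessment, Sample Size and Sampling Procedure have been reconciled and confirm 12 cohort subdistricts.

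The cost is a change of wording and a few individual-level parameters estimated from several hundred infants. No new data, participants or cluster-level degrees of freedom are needed for the height term. The optional subdistrict term would use one cluster-level degree of freedom.

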### Research Ethics

We obtained ethical approval for the study from the Faculty of Public Health, University of Indonesia (323/H2.F10/PPM.00.02/2016) and the Human Research Ethics Committee of the University of Sydney (Protocol number: 2015/115). Trained field staff carefully explained the background and objectives of the study to the women and gave a written information sheet to all women contacted. We obtained written informed consent from the women who agreed to participate in the study. We will maintain the privacy, anonymity, and confidentiality of the information provided by respondents during all phases of the study. We will store all information in an encrypted database with the participant’s study identifier instead of personal identifiers, and only the investigators and authorized data management team will have access to the data collected.

### Data Monitoring

On the basis of the CommCare data capture system, we will design a real-time study monitoring information system to provide information on enrolment status, adherence of the data collectors to the evaluation schedule, and the quality of key data elements. The system will generate automated emails to distribute information to field supervisors. Field supervisors will use this system to monitor the performance of individual data collectors, and all reports will be available for review by the investigators.

### Data Access

All data collected will be accessible to the study investigators, who will have the right to analyze and publish data. We will make the relevant anonymized individual-level data available on reasonable request.

## Results

### Cross-Sectional Evaluation

We conducted the baseline survey for the cross-sectional evaluation in February 2015. We recruited 2435 mothers and their children aged <2 years, of whom 1199 were in the intervention group and 1236 were in the comparison group. Similarly, we recruited 409 pregnant women, of whom 198 were in the intervention group and 211 were in the comparison group.

We conducted the end-line survey in February 2017. We recruited 2740 mothers and their children aged <2 years, of whom 1357 were in the intervention group and 1383 were in the comparison group. Similarly, we recruited 642 pregnant women, of whom 306 were in the intervention group and 336 were in the comparison group.

### Cohort Evaluation

We began recruitment to the cohort evaluation in February 2015 and completed the follow-up of participants in December 2016. We screened 729 pregnant women for their eligibility to join the study, of which 685 mothers (343 in the control group and 342 in the intervention group) who delivered their babies were followed up in the study till the child was 18 months old. Among them, 331 in the control group and 327 in the intervention group remained in the study until the end. There were 12 dropouts in the control group and 15 dropouts in the intervention group.

We completed data cleaning and processing for both evaluations in July 2017, followed by analysis, report writing, and dissemination of the results.

## Discussion

### Overview

Childhood undernutrition remains a global public health nutrition problem, with an estimated 150 million children worldwide with stunted linear growth, despite recent progress made to improve the nutritional status of children [52]. Although Indonesia is a middle-income country, it is ranked 25th globally for its prevalence of childhood stunting and fifth for the number of stunted children [53]. Furthermore, the prevalence of stunting among children aged <5 years in Indonesia between 2007 and 2013 has remained stagnant at 36%-37% [54]. The Government of Indonesia has established nutrition development targets and aims to reduce the prevalence of stunting among children aged <2 years from 33% in 2013 to 28% in 2019 [22]. Strong evidence is needed about effective intervention packages to reduce stunting to guide policy and program decisions at the national level and for the decentralized district governments. This paper describes a study protocol of a cluster randomized controlled study to assess the impact of a package of behavior change interventions and health system strengthening activities on maternal and child nutrition status.

### Limitations

We designed the study to examine the impact of the package of Baduta nutritional and behavioral change interventions on the primary outcome, child stunting; therefore, we cannot identify the impact of the individual behavior change intervention components. We measured the exposure to the interventions in the end-line survey for the cross-sectional evaluation and at the end of the follow-up period at 18 months in the cohort evaluation. This information is for process evaluation, but we may use it to examine the associations between the individual intervention components and child growth in analytical epidemiological analyses.

The small number of clusters in which it was feasible to implement the interventions, especially the health systems interventions, prevented the use of simple randomization to allocate the treatments. We addressed this study design limitation through the use of restricted randomization [26,30] in which we used existing village census and health surveillance information to identify the set of combinations of the study subdistrict clusters that had a balance of characteristics or indicators that were related to the study outcomes. We randomly selected one of these balanced combinations to allocate study treatments.

A further limitation of the study is the lack of an economic analysis to assess the cost-benefit of the program for preventing child stunting.

### Study Implications

In Indonesia, reaching the current nutrition targets for child stunting will require an integrated approach that includes support for appropriate IYCF practices, including exclusive breastfeeding for 6 months, continued breastfeeding for 2 years, timely and appropriate complementary feeding, improved maternal nutrition, access to quality health services, water and sanitation, and other public health measures. The results of this study will provide valuable inputs for future research on preventing child stunting and help to formulate and guide policies to support effective packages of nutrition behavior change interventions to prevent child stunting in Indonesia.

## Appendix

Multimedia Appendix 1 Map of Baduta impact evaluation districts in East Java.

Multimedia Appendix 2 Description of emo-demo sessions.

Multimedia Appendix 3 Emo-demo visuals.

Multimedia Appendix 4 Description of the four TV spots.

Multimedia Appendix 5 Baduta behaviour change messages in poster format.

## Abbreviations

24-HR: 24-hour dietary recalls
DHS: Demographic and Health Survey
GAIN: Global Alliance for Improved Nutrition
Hb: hemoglobin
IYCF: infant and young child feeding
SEAMEO-RECFON: Regional Centre for Food and Nutrition, Southeast Asian Ministers of Education Organization
UNICEF: United Nations Children’s Emergency Fund
WHO: World Health Organization
